## Abstract

**Introduction:**

Circadian regulation modulates metabolic and hormonal processes throughout the day, yet it remains unclear whether these diurnal fluctuations are reflected in exhaled volatile organic compound (VOC) profiles and whether such temporal patterns differ between individuals with and without diabetes. Previous breath analysis studies in diabetes have shown heterogeneous results, which may reflect differences in analytical approaches and the lack of standardised sampling times.

**Methods and analysis:**

This prospective, single-centre observational study examines daytime VOC dynamics from 08:00 to 16:00 among adults without diabetes, and individuals with type 1 diabetes or type 2 diabetes. 60 participants will complete one in-person visit with repeated breath measurements using a BreathSpec^®^ gas chromatography–ion mobility spectrometry system (GC-IMS) device, capillary glucose testing, body composition assessment, questionnaires, and oral and stool microbiota sampling. A standardised breakfast is provided; subsequent meals follow structured timing but are not standardised. The primary outcome is temporal variation in VOC intensities. Secondary outcomes include between-group differences and associations with glucose levels, body composition and microbiota composition. Analyses will use established GC–IMS tools and exploratory multivariate approaches.

**Ethics and dissemination:**

Ethics approval was granted by the Ethics Committee of the Canton of Bern (BASEC 2023-01143). Results will be shared via peer-reviewed publications, conferences and lay summaries.

**Trial registration number:**

NCT05984979.

STRENGTHS AND LIMITATIONS OF THIS STUDYControlled yet pragmatic single-day design enables assessment of daytime variation in exhaled volatile organic compounds (VOCs) under near-real-world conditions.Inclusion of participants without diabetes, with type 1 diabetes and with type 2 diabetes enables cross-group comparison of metabolic influences.Multimodal sampling (breath VOCs, glucose, body composition, oral and stool microbiota) supports integrative analyses.Exploratory nature and modest sample size limit formal inference; findings will primarily inform future powered studies.Dependence on a single gas chromatography–ion mobility spectrometry system instrument introduces vulnerability to device downtime and scheduling delays.

## Introduction

 Breath volatile organic compounds (VOCs) arise from endogenous metabolism, microbial activity and environmental exposures, and have been evaluated as non-invasive markers in metabolic and inflammatory contexts.^1^,^4^ In diabetes research, altered levels of VOCs such as ethanol, isopropanol, dimethyl sulfide, isoprene and pentanal have been reported in individuals with type 1 diabetes (T1D) compared with individuals without diabetes.^5^ Other studies suggest associations between exhaled acetone, methyl nitrate, methanol, propane and circulating glucose,^6^ and hypoglycaemia-linked breath signatures have been observed.^7 8^ However, these findings are not uniform. Some investigations identified glucose–acetone correlations, whereas others did not.^9 10^ Heterogeneity in analytical platforms, diet, gut microbiota composition and function, metabolic status and sampling procedures likely contributes to these inconsistencies.^11^ Despite these limitations, breath VOC analysis holds potential as a non-invasive adjunct to existing biomarkers, offering real-time metabolic information relevant to glycaemic monitoring, early detection of dysglycaemic states, disease stratification and potentially early identification of metabolic dysregulation in populations at risk for or with undiagnosed type 2 diabetes (T2D),^11 12^ though superiority over established markers has not yet been demonstrated.

Circadian physiology may also influence breath VOC patterns. Hormonal rhythms, eating behaviour, nutritional composition and microbial metabolism vary across the day.^11^,^14^ Breath studies in respiratory medicine have shown time-of-day differences in specific exhaled metabolites.^15^ Yet, in diabetes research, sampling times are rarely standardised, and circadian effects are seldom considered.^5^,^79 10^ If temporal variation exists, ignoring it may obscure clinically meaningful signals; if minimal, sampling may be more flexible than assumed.

This study investigates whether breath VOC profiles show daytime variation under controlled but pragmatic conditions. We focus on an 8-hour window (08:00–16:00) with fasting at entry, a standardised breakfast and structured breath-sampling intervals. The aim is to characterise temporal patterns in exhaled VOCs in adults with T1D and T2D and those without diabetes, and to explore associations with glucose, body composition and oral and stool microbiota composition. Findings from this exploratory work may support more informed design of breath-based metabolic monitoring studies.

To address these objectives, we designed an observational protocol with predefined sampling frequency, dietary timing and analytic steps. The sections below describe the study procedures and statistical plan.

## Methods and analysis

### Study design and setting

This prospective, single-centre observational study is conducted in the clinical study facilities at the Diabetes Center Berne (DCB), Switzerland. Each participant completes one 8-hour study visit. The study aims to estimate daytime breath VOC dynamics rather than test a formal intervention or treatment effect.

Recruitment began in 2023, with data collection completed for three participants. The study has been paused since June 2024 due to device unavailability and resumed in December 2025. No interim analyses have been conducted to date. Enrolment is expected to conclude by October 2026, with primary data analysis completed within approximately 6 months thereafter.

### Participants and eligibility

Three adult groups are enrolled: individuals without diabetes, those with T1D and those with T2D. Participants must be ≥18 years old. Individuals with T1D must have a diagnosis for ≥1 year and use multiple daily injections or insulin pump therapy. The no-diabetes group requires no clinical diagnosis of diabetes and glycated haemoglobin (HbA1c) <6.5%. The T2D group requires a documented medical diagnosis with HbA1c>6.5% and treatment with oral antidiabetic medication and/or insulin therapy. Recruitment aims for approximate balance by sex and by body mass index (BMI) category (<25 kg/m² vs ≥25 kg/m²) as specified in the protocol, but groups are not randomised or strictly stratified by these variables.

Key exclusions (applied across all groups) include pregnancy or breastfeeding; smoking within 6 months; chronic pulmonary or intestinal disease (eg, asthma, Chronic obstructive pulmonary disease (COPD), Inflammatory bowel disease (IBD)); coeliac disease; lactose or fructose intolerance; acute infection; current use of inhaled medicines; antibiotic treatment within the previous 4 months; and daily alcohol consumption >4 units.

Potential confounders (eg, recent diet, sleep, physical activity, recent or mild intercurrent infections not meeting exclusion criteria, medication changes and environmental exposures) are documented via diaries and questionnaires for descriptive adjustment in analyses. Socioeconomic factors are not systematically controlled in this exploratory protocol and are noted as limitations. All eligibility criteria are summarised in table 1.

**Table 1 T1:** Eligibility criteria

Group	Criteria
All participants	Age ≥18 years; able to provide written informed consent
No diabetes	No clinical diabetes diagnosis; HbA1c <6.5%
Type 1 diabetes (T1D)	Documented T1D; insulin therapy (MDI or CSII) ≥1 year
Type 2 diabetes (T2D)	Documented T2D; HbA1c >6.5%; oral agents and/or insulin therapy
Exclusion (all groups)	Pregnancy/breastfeeding; smoking within 6 months; chronic pulmonary or intestinal disease (eg, asthma, COPD, IBD); coeliac disease; lactose or fructose intolerance; acute infection; current inhaled medicines; antibiotics within 4 months; alcohol >4 units/day

COPD, Chronic obstructive pulmonary disease; CSII, continuous subcutaneous insulin infusion; HbA1c, glycated hemoglobin; HbA1c, glycated haemoglobin; IBD, Inflammatory bowel disease; MDI, multiple daily injection.

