### Data processing and analysis

Data are processed using VOCal (GAS Dortmund) with retention index libraries (eg, NIST2020) and drift-time alignment. Analysis uses Python (gc-ims-tools) and R. Temporal VOC intensity profiles will be characterised descriptively across the 08:00-16:00 window, and within-subject changes over time will be assessed using non-parametric repeated-measures approaches appropriate for the data structure. Gallery plots will support visual inspection of spectral patterns. Between-group comparisons will include both overall group differences and exploratory pairwise comparisons (no diabetes vs T1D, no diabetes vs T2D, and T1D vs T2D), using appropriate non-parametric tests (eg, Wilcoxon rank-sum or Kruskal-Wallis). Given the exploratory design and limited consistency in prior findings, no single comparison is prioritised a priori. Associations between VOCs and capillary glucose, body composition and microbiota composition will be assessed using correlation analyses, including repeated-measures correlation for intraindividual relationships. For between-group VOC discrimination, supervised multivariate methods including Partial Least Squares Discriminant Analysis (PLS-DA) and Support Vector Machine (SVM) may be applied as exploratory tools, building on approaches previously used with GC-IMS breath data in this study population.^8^ Principal component analysis supports dimensionality reduction and visual exploration of VOC patterns. No imputation is planned.

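### The plan speaks of adjusting for confounders, but the group tests and cross-sectional correlations it names take no covariates, and age is neither balanced nor listed

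*Protocol article*

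**What the plan says.** All places are in the protocol article, Methods and analysis.

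- **Participants and eligibility, on adjustment.** Confounding factors, the article says, "are documented via diaries and questionnaires for descriptive adjustment in analyses". The phrase is not defined further. The factors are given only by example: "Potential confounders (eg, recent diet, sleep, physical activity, recent or mild intercurrent infections not meeting exclusion criteria, medication changes and environmental exposures").
- **Participants and eligibility, on balance.** "Recruitment aims for approximate balance by sex and by body mass index (BMI) category", with BMI split at 25 kg/m², "but groups are not randomised or strictly stratified by these variables". The only rule on age is "Participants must be ≥18 years old".
- **Data processing and analysis.** Group comparisons, overall and for all three pairs, are made "using appropriate non-parametric tests (eg, Wilcoxon rank-sum or Kruskal-Wallis"). Associations with glucose, body composition and microbiota use correlation analyses, with repeated-measures correlation for the within-person part. PLS-DA and SVM are optional, and no covariates are mentioned for them.
- **Outcomes (Table 4).** The primary outcome is variation of VOC intensity over the day. Group comparisons and associations are secondary.
- **Data sources (Table 3).** Demographics and body composition are collected.
- **Study design and setting.** Three participants had been measured before the pause: "The study has been paused since June 2024 due to device unavailability and resumed in December 2025".

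**The concern.** Two parts of the same article do not meet. One says that confounders will be adjusted for in some descriptive sense. The other names methods that, in their usual form, have no place for a covariate.

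Age is the clearest exposure. Adults of any age may enter any group, nothing aligns the groups on age, and age is missing from the example confounders. If the no-diabetes, T1D and T2D groups differ in age, and a VOC varies with age, the unadjusted contrast carries that difference.

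Sex and BMI are in a better position because recruitment aims to balance them. The balance is approximate, however, is not said to hold within each group, and uses a single BMI cut, so adiposity can still differ between groups inside a category. A correlation of a VOC with body composition pooled over the three groups can then partly reflect group membership.

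The Discussion says that the study should supply effect size estimates for later studies. Confounding biases those estimates whether or not anyone reads the p-values.

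**Working it through.** **Inputs from the article.** Up to 60 participants in three groups, about 10 per group at first. 60 / 3 = 20 per group if the groups end up equal (an assumption). The article gives no alpha, power, effect size or SD, so it has no figure of its own to reproduce on this point.

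**Assumptions, because the article gives neither value.** The VOC-age correlation within group, r, is 0.2 to 0.5. The difference in mean age between two groups, g, is 0 to 1.5 within-group SDs. There is no disease effect, the data are normal, and tests are two-sided at 5%.

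**Bias.** If VOC = r × age + noise, with both scaled to SD 1 within group, the expected unadjusted group difference is g × r. The smallest non-zero case is 0.5 × 0.2 = 0.10 SD and the largest is 1.5 × 0.5 = 0.75 SD. All of it is due to age.

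**False positives of the unadjusted rank-sum test** (3,000 simulated studies per cell; the zero-gap case was run at r = 0.3 only):

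| Age gap g | Per group | r = 0.2 | r = 0.3 | r = 0.5 |
|---|---|---|---|---|
| 0 | 20 | – | 4.6% | – |
| 0.5 SD | 20 | 6.1% | 8.0% | 11.5% |
| 1 SD | 20 | 10.3% | 13.8% | 32.5% |
| 1.5 SD | 20 | 14.7% | 26.9% | 62.8% |
| 0 | 10 | – | 4.4% | – |
| 0.5 SD | 10 | 4.2% | 4.9% | 7.4% |
| 1 SD | 10 | 6.4% | 9.3% | 17.4% |
| 1.5 SD | 10 | 7.9% | 15.4% | 33.2% |

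**Hand check of one cell.** The normal approximation to the rejection rate is Φ(g·r·√(n/2) − 1.96), ignoring the far tail. With n = 20, g = 1 and r = 0.5, this is Φ(0.5 × 3.162 − 1.96) = Φ(−0.379) = 35%. The simulated rank test gives 32.5%, slightly lower, as expected for a rank test.

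**With age in the model.** A linear model with group and age, correctly specified here, rejects in 4.3% to 5.8% of studies over all settings. A rank-transformed ANCOVA with 20 per group, at gaps of 1 and 1.5 SD and r of 0.3 and 0.5, rejects in 5.0% to 6.2%.

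**Instrument period.** Three of 60 is 5%. In the worst case all three are in one group of 20, which is 15% of it. A shift of 1 to 3 SD then gives a bias of 0.15 × 1 = 0.15 SD to 0.15 × 3 = 0.45 SD, and 6-9% false positives (5,000 runs per setting). If one falls in each equal-sized group, the bias is zero.

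**The case against.** The strongest reply has five parts.

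1. *This belongs in the analysis plan.* A condensed article may leave covariate lists to a fuller document, and one may exist. That stands for the detail of a model. It does not remove the mismatch inside the article between a stated adjustment and the methods named for it; an analysis plan that followed the article would carry the gap forward.

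2. *The lists are open.* Both the confounders and the tests are given as examples. Rank methods have stratified forms, a partial rank correlation is still a correlation analysis, and the adjustment is called descriptive. This stands. A reader might infer that the plan rules out any adjustment. The text supports less: the named methods provide none, and no other step is described.

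3. *Confounders are not all alike.* A reader might put sex, BMI and instrument period beside age. The article does not support that. Sex and BMI category are recruitment targets. For the instrument, it reports unavailability of the device but no change of it, does not give the groups of the three early participants, and specifies drift-time alignment and retention-index libraries. Only a minor possibility remains.

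4. *The study is exploratory and its primary outcome is within-person.* This limits the reach. Stable traits such as age cancel in within-person change and in repeated-measures correlation; time-varying confounders do not. A reader might conclude that the study as a whole cannot be interpreted; that does not follow. A comparison of such changes between groups is again between persons, and age can enter it. The absence of formal testing makes the bias in SD units the more relevant measure than the 5% rejection rate.

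5. *An ANCOVA on age, sex and BMI leaves the listed diary items unadjusted.* True. With 10 to 20 per group only a few covariates can be carried, so those items are better tabulated by group, which may be all that the phrase intends.

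**Conclusion.** The point holds for the secondary group comparisons and for the cross-sectional correlations of VOCs with body composition and microbiota. The stated adjustment has no counterpart among the named methods. Age is unaddressed, and adiposity is only partly controlled.

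The bias is the age gap times the VOC-age correlation. With 20 per group and correlations of 0.2 to 0.5, false positives are about 6-12%, 10-33% and 15-63% at gaps of 0.5, 1 and 1.5 SD. They are about 4-5% with no gap, and about 4-6% once age is in the model. The inflation is smaller with 10 per group. These figures show what could happen under assumed values; the article gives neither the gap nor the correlation, so they do not show that the groups will differ in age.

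The change is worth making because it is cheap and can still be prespecified: enrolment is expected to run to October 2026, and no interim analysis has been done.

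**What to change.** 1. **Group comparisons.** Keep the unadjusted rank tests. Beside them, report an ANCOVA on rank-transformed values or log intensities, using one summary per participant, such as the fasting value or the change over the day, so that the temporal question is kept. Include group, age, sex and continuous BMI. Show it with and without BMI, because BMI is tied to T2D and adjusting for it may remove part of the contrast of interest.
2. **Body composition and microbiota.** Use partial rank correlations given group, age and sex. Repeated-measures correlation for glucose can stay as it is.
3. **Diary and questionnaire items.** Say what descriptive adjustment means; a table of these items by group would do.
4. **Alternative.** If no adjusted analysis is wanted, withdraw the word adjustment and label all group differences and pooled correlations as unadjusted.
5. **Optional minor check.** Repeat the group analyses without the three participants measured before the pause.

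Cost: wording only, with no new data, since demographics and body composition are already collected. The adjusted model spends about three degrees of freedom, and its intervals will be wider where the groups' ages overlap little. That width is informative, since it shows how far the data can separate disease status from age.

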### Recruitment and consent

Recruitment occurs through flyers, local clinics, doctors’ offices and online postings. Interested individuals complete an initial self-screen. The study team confirms eligibility. Written informed consent is obtained before procedures. Participants receive 100 CHF compensation.

### Study procedures

Participants are instructed to fast from midnight before the study visit and to abstain from alcohol for 24 hours prior to the visit. On the morning of the visit, they are asked to avoid using toothpaste and mouthwash for at least 1 hour before the first measurement and, if possible, to refrain from using cosmetic products such as make-up, shampoo or perfume.

At 08:00, participants complete questionnaires (36-Item Short Form Health Survey (SF-36), International Physical Activity Questionnaire (IPAQ)) and undergo bioimpedance body composition analysis (BIA; InBody 770). HbA1c is measured on site only if no recent result (<3 months) is available from the patient record, using a DCA Vantage analyser (Siemens) according to the manufacturer’s instructions. Two fasting breath samples and one capillary glucose measurement are then collected. Participants subsequently provide an oral microbiota swab and consume a standardised breakfast (YFood shake providing 200 kcal: 15 g carbohydrates, 12.5 g protein, 8 g fat and 3 g fibre).

Breath VOC and glucose samples are collected every 15 min for approximately 90 min. For the remainder of the day, participants may consume self-selected meals or snacks according to their usual routine, with breath VOC and glucose sampling immediately beforehand. An overview of the study schedule is illustrated in figure 1, and the schedule is summarised in table 2.

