**Figure 1 F1:**
[figure not shown]
Schematic measurement schedule. Participants arrive fasting at 08:00, complete baseline assessments and consume a standardised breakfast. Breath VOC and capillary glucose samples are collected at fasted baseline and every ∼15 min during the first postprandial period. Subsequent meals (meals 2–4) are not standardised and are consumed voluntarily; breath VOC and glucose samples are collected immediately before each eating episode. VOC, volatile organic compound.

**Table 2 T2:** Schedule of study procedures

Procedure	Previsit	Visit day
Eligibility screening	X	
Informed consent	X	
Fasting and preparation instructions	X	
Diet and sleep diary (covering 2 days before visit)	X	Return (on or after visit)
Stool sample kit (collection within ±2 days)	X	Return (on or after visit)
Questionnaires (SF-36, IPAQ)		X
Body composition (BIA)		X
Oral microbiota swab		X
HbA1c (if not available <3 months in patient records)		X
Baseline breath VOC and capillary glucose		X
Standardised breakfast		X
VOC and glucose every 15 min (first 90 min)		X
VOC and glucose before subsequent meals/snacks		X

BIA, Bioelectrical Impedance Analysis; IPAQ, International Physical Activity Questionnaire; SF-3, 36-Item Short Form Health Survey; VOC, volatile organic compound.

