## Discussion

This study examines whether daytime changes in exhaled VOCs can be observed under controlled, real-world-compatible conditions and whether such changes differ across metabolic groups. Breath signatures in diabetes have shown promise, but reproducibility challenges remain. Time-of-day effects are plausible contributors and have not been systematically explored in diabetes research. A standardised breakfast and structured sampling allow evaluation of short-term metabolic responses, while participant-selected meals later in the day preserve ecological validity.

This work is exploratory and not powered for formal hypothesis testing. Instead, the intent is to generate data on temporal variation, effect size estimates and protocol considerations for future studies. Insights regarding sampling windows, fasting requirements and links to glucose or microbiota profiles may help refine breath-based metabolic monitoring approaches. If meaningful daytime variation emerges, time-locked sampling may be warranted; if not, breath analysis may offer greater flexibility than currently assumed.

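### The dense post-breakfast breath series cannot separate volatiles of the shake itself from metabolic or time-of-day change, and 3 to 4 of its 6 nominal samples fall within 1 hour of the shake

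*Protocol article*

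**What the plan says.** All places are in the Protocol article.

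- **Preparation (Study procedures).** "Participants are instructed to fast from midnight before the study visit". Participants are also asked to "avoid using toothpaste and mouthwash for at least 1 hour before the first measurement".
- **Baseline (Study procedures).** "Two fasting breath samples and one capillary glucose measurement are then collected".
- **Breakfast (Study procedures).** After an oral swab, all participants "consume a standardised breakfast (YFood shake providing 200 kcal", with one fixed composition.
- **Post-breakfast series (Study procedures; also Table 2).** "Breath VOC and glucose samples are collected every 15 min for approximately 90 min".
- **Later samples (Figure 1 legend).** "Subsequent meals (meals 2–4) are not standardised and are consumed voluntarily"; for these, "breath VOC and glucose samples are collected immediately before each eating episode".
- **Use of the samples.** The primary outcome is the profile of VOC intensity over the whole 08:00 to 16:00 window (Outcomes). At about 30 participants the study stops unless circadian intensity changes are seen in at least three VOCs (Sample size). Within-person change over time and repeated-measures correlations are planned (Data processing and analysis). The Discussion gives the purpose of the early series: "A standardised breakfast and structured sampling allow evaluation of short-term metabolic responses".

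**The concern.** The baseline breath comes from a mouth kept free of food and oral-care products. The next breath samples come from a mouth that has just held a food product. Only the breakfast series is scheduled to follow food in this way; later samples are timed before eating. If volatiles of the shake reach the instrument, a peak can appear after breakfast and decay with no metabolism involved.

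Three features make this matter.

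- The product is identical for everyone, so any residual signal would have the same direction and similar timing in all participants. It would not average out with more participants and would look like a highly reproducible pattern.
- The affected samples are the densest part of the primary outcome and also feed the interim rule. Shake peaks would push that rule towards continuing.
- Glucose is measured alongside these breath samples. Residue that fades while glucose is also changing could produce a within-person VOC-glucose correlation with no metabolic link.

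Modelling time since breakfast would not solve this, because residue and metabolism share that time axis.

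**Working it through.** The article states no sample count or share on this point, so there is no figure to reproduce. The check is a count of sampling times.

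**Inputs**

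- Interval 15 min, duration about 90 min (Study procedures, Table 2).
- Two fasting breath samples before breakfast (Study procedures).
- 0 to 3 later pre-meal samples, for voluntary meals 2 to 4 (Figure 1 legend).
- Reference interval of 60 min, borrowed from the toothpaste and mouthwash instruction. Applying it to food is my assumption.
- Clock starting at the end of breakfast, first sample at 15 min. Both are assumptions and are varied below.

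**Share of the 90-min series**

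Nominal times: 15, 30, 45, 60, 75, 90 min, so 90/15 = 6 samples.

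- Less than 60 min: 15, 30, 45, so 3/6 = 50%.
- At or below 60 min: 15, 30, 45, 60, so 4/6 = 67%.
- With an extra sample at 0 min: 4/7 = 57% and 5/7 = 71%.

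**Share of all post-breakfast samples**

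Share = k / (n + m), where k is the number within the hour, n the size of the series and m the number of later pre-meal samples.

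| Later samples (m) | Grid from 15 min, <60 | Grid from 15 min, ≤60 | Grid from 0 min, <60 | Grid from 0 min, ≤60 |
|---|---|---|---|---|
| 0 | 3/6 = 50% | 4/6 = 67% | 4/7 = 57% | 5/7 = 71% |
| 1 | 3/7 = 43% | 4/7 = 57% | 4/8 = 50% | 5/8 = 63% |
| 2 | 3/8 = 38% | 4/8 = 50% | 4/9 = 44% | 5/9 = 56% |
| 3 | 3/9 = 33% | 4/9 = 44% | 4/10 = 40% | 5/10 = 50% |

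**Share of the time-fixed samples**

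Two fasting plus six post-breakfast samples make 8: 3/8 = 38% and 4/8 = 50%.

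**If the clock starts when drinking begins**

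Subtract the drinking time d from each sample time. For d of 5, 10 or 15 min, 4 of 6 samples are less than 60 min after the last sip. At or below 60 min the count is 4, 4 and 5 of 6. The count rises slightly and the conclusion does not change.

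**What remains if samples within the hour are set aside**

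On the grid from 15 min, the samples at 60, 75 and 90 min remain: 2 fasting + 3 + m later = 5 to 8 breath samples per participant for m = 0 to 3, against 2 + 6 + m = 8 to 11 in the full set.

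These figures count samples near the shake. They do not measure bias: the article does not say how long residue persists, whether it reaches the GC-IMS signal, or which peaks it would touch.

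**The case against.** The strongest case against has five parts.

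1. **The 1-hour instruction is not a washout for food.** It names toothpaste and mouthwash and applies before the first measurement only. Food has its own rule, the overnight fast, and the shake is given deliberately after baseline. A reader might infer that the schedule breaks the protocol's own washout. The document does not support that: nothing is contradicted, and it gives no reason for the instruction. This stands; the hour is an analogy only.
2. **Contamination is not shown.** A reader might infer that shake residue will be counted as VOC variation. Without data on persistence or affected peaks, one can say only that it could be. This stands.
3. **The share depends on the denominator.** A reader might infer that at least half of all post-breakfast samples are affected. That is assured only for the 90-min series. This stands.
4. **A rinse or product blank may be in the full protocol.** The article gives breath collection one sentence (VOC and biospecimen collection), so silence on this is not a finding. This stands.
5. **The study is exploratory, and its outcome is not limited to endogenous compounds.** The Introduction itself lists environmental exposures among VOC sources. This is true of the descriptive profile. It does not help where the plan attaches a meaning to the change: the interim rule counts circadian changes and the Discussion speaks of metabolic responses. Both readings require that the change not come from the product.

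So the objections narrow the claim. They leave the fixed timing and the interpretation placed on it.

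**Conclusion.** The point holds as a risk of misattribution of unknown size. The baseline is protected from oral products, while 3 to 4 of the 6 nominal samples in the densest part of the primary outcome lie within 1 hour of an identical shake. On that grid with three later meals, this is 33 to 44% of all post-breakfast samples. As described, the design cannot separate product volatiles from metabolic or time-of-day change, so such peaks can enter the temporal profile, the metabolic reading and the three-VOC rule.

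The counts assume nominal 15-min timing from the end of breakfast, a first sample at 15 min, and the borrowed 60-min reference. Other start conventions leave at least half of the 90-min series within the hour. A change is worth making but does not put the study in doubt.

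**What to change.** 1. Run the shake's headspace once on the same BreathSpec and flag every peak found in it.
2. State that a flagged peak does not count towards the three-VOC interim rule, and is not called a metabolic or circadian change, unless the change also appears in a sensitivity analysis restricted to fasting samples and samples at least 60 min after breakfast.
3. Keep all early samples in the descriptive profile, with flagged peaks marked.
4. If the full protocol does not already have one, a water rinse after the shake may be added. Record whether the three completed participants (Study design and setting) had it.

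**Cost.** One instrument run, a few lines of analysis text and possibly a rinse. The flags also apply to the three completed participants. Claims for some flagged VOCs would rest on fewer time points, 5 to 8 instead of 8 to 11 per participant. A compound present in the shake may also be produced by metabolism, so a real early response in it could go unclaimed. For that reason I would not drop flagged peaks outright or make the 60-min cut-off the main analysis. The fix deals only with product volatiles; it does not separate a genuine meal response from time of day.
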